#### Urine sampling

3.2.2

During IP1 and IP2, two urine samples are collected from each participant, the first on Monday morning of Week 1 and the second on Friday afternoon of Week 2 (Figure 7). To directly correlate their external exposure to internal dose, a stratified, data-driven strategy is employed for targeted biomarker analysis. The selection of urinary biomarkers of exposure will be informed by the results of the preceding air samplings. For example, if certain compounds (e.g., benzene or pyrene) are consistently detected or show significant variance during the air sampling campaigns, their corresponding specific biomarkers of exposure (e.g., SPMA for benzene and 1-OHP for pyrene) will be quantified via GC–MS or LC–MS/MS. This allows for precise assessment of children’s internal dose and direct correlation with the measured school environment. Additionally, samples will be screened for general biochemistry and contaminants. Country-specific protocol variations apply, as ethical and regulatory restrictions preclude urine collection in Greece. To address the impact of these biomonitoring variations across cohorts, environmental monitoring will serve as the primary, standardized exposure metric to link with health outcomes (as described in Section 4) for pooled exposure-response analyses of the entire cohort across the three countries. Analyses relying on urinary biomarkers will be stratified and limited to the Belgian and Danish cohorts to further investigate internal exposure pathways and complement environmental data.

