
Children perform the cognitive tests at four time points (Figure 7). During the BaP, each child completes all cognitive tests twice on different days to account for potential learning curve effects (57). Afterward, the children repeat the tests during the intervention and sham-intervention phases on the testing days to evaluate the impact of IAQ. To control for any residual learning effects, the specific intervention period will be included as a covariate in the mixed-model analysis. Cognitive testing is standardly performed between 08:00 and 12:00 h to account for variations in concentration dependent on the time of day (58, 59). The supervisor documents possible distractions and lapses in concentration. Children are given a score based on their attentiveness during the cognitive testing (0 = no problem, 1 = distracted, 2 = influenced by someone, 3 = external distractions, 4 = did not understand the task, 5 = bored, 6 = other). A score is assigned for each of the cognitive tests. Reasoning for the score is also noted down.

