### Statistical strategy

5.3

Descriptive statistics will be used to summarize participant, classroom, and school characteristics; indoor air pollutant levels; microclimate parameters; biomarker concentrations; cognitive performance; and health outcomes.

To evaluate the impact of the intervention (vs. sham-intervention) and IAQ on longitudinal child outcomes, specifically cognitive performance and clinical/biological parameters (e.g., blood pressure), linear mixed-effects models will be applied. This model is specifically chosen to account for the longitudinal nature of the data, as multiple measurements will be collected from the same child. To handle the hierarchical clustering, random intercepts will be specified for school, class, and child. Background variables will be included as fixed-effect covariates in the models. Questionnaire data and clinical/pollution measurements will provide the necessary parameters to adjust for individual (e.g., socioeconomic factors and anthropometric measurements) and environmental (e.g., classroom pollution exposure, season) confounders, selected according to the requirements of each distinct analysis. Data collected from pre-sampling screening questionnaires will be used to adjust for building characteristics (e.g., building age, ventilation system) and external environmental factors (e.g., traffic exposure).

To analyze differences in environmental exposure levels (both external pollutants and internal exposure parameters) across different study phases (intervention vs. sham-intervention) and subgroups (e.g., schools), paired statistical tests (e.g., Student’s t-test, Mann–Whitney U test, or Wilcoxon signed-rank test) and ANOVA (or Kruskal-Wallis test, or Friedman test) will be used. The relationship between various parameters will be statistically analyzed using correlation and regression analysis.

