A fourth strength is the comprehensive environmental measurements, including VOCs and aldehydes, during the “Intervention Periods.” Unlike previous studies that only selected one approach for sampling duration, we perform continuous passive air sampling throughout the school hours, during the whole week (except weekends), in combination with active sampling 3 days per week during school hours. This design allows for the evaluation of overall and daily changes in levels of VOCs and aldehydes during each “Intervention Period,” and their potential relationships with classroom activities, weather, and other parameters. The dual sampling approach also allows us to avoid potential over- or underestimation of VOCs and aldehydes concentrations due to the inclusion of unoccupied periods in the sampling interval, as seen in previous studies (44, 67).

A fifth strength is that two urine samples are collected on Monday morning and Friday afternoon, respectively, to distinguish between school/home exposures. Monday’s samples are collected after being at home over the weekend to reflect primarily home-based exposure, whereas Friday’s samples are collected after 5 days of school (and at home in the evening) to reflect the integrated exposure at home and school. By comparing biomarker levels between the samples from these two time points, the effects of school-specific exposures and interventions can be more accurately assessed, minimizing confounding by home or out-of-school exposures.

On the other hand, there are also some limitations. A notable limitation is the exclusion of children and/or guardians with insufficient local language proficiency, which was logistically necessary to ensure the accurate completion of questionnaires and cognitive assessments. However, this criterion may introduce selection bias and limit the overall representativeness of the study population. Specifically, it potentially underrepresents certain vulnerable groups, such as children from recently immigrated families.

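### The Monday-morning versus Friday-afternoon urine contrast cannot by itself be attributed to school exposure, because it is fully aliased with time of day and weekday

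*Protocol article*

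**What the plan says.** Section 3.2.2 of the protocol article (Urine sampling) has each child give two urine samples in IP1 and again in IP2: "the first on Monday morning of Week 1 and the second on Friday afternoon of Week 2".

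Section 6.2 presents this as the fifth strength of the study: "two urine samples are collected on Monday morning and Friday afternoon, respectively, to distinguish between school/home exposures". The Monday "samples are collected after being at home over the weekend to reflect primarily home-based exposure", while the Friday "samples are collected after 5 days of school (and at home in the evening" and are said to reflect home and school together. The conclusion drawn is this: "By comparing biomarker levels between the samples from these two time points, the effects of school-specific exposures and interventions can be more accurately assessed", with confounding from the home and other places outside school kept to a minimum.

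Section 5.3 plans paired tests and ANOVA-type tests of external and internal exposure levels "across different study phases (intervention vs. sham-intervention) and subgroups (e.g., schools". Sections 2.2 and 5.3 also plan linear mixed models for biological parameters, with random intercepts for school, class and child.

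**The concern.** The first sample is always a Monday-morning sample and the second always a Friday-afternoon sample. No child gives a Monday-afternoon or Friday-morning sample, so anything that differs between those two moments for reasons other than the classroom (time of day, hydration, diet, weekday routine) falls into the difference that Section 6.2 reads as school exposure.

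Elsewhere the article guards against this. Section 4.3 states: "Cognitive testing is standardly performed between 08:00 and 12:00 h to account for variations in concentration dependent on the time of day". Section 4.2 holds blood pressure to the same 08:00 to 12:00 window, and Section 3.2.1 holds blood sampling to 12:00 to 14:00. Urine is the one measure whose two compared samples fall in different parts of the day, and the limitations in Section 6.2 do not mention it.

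Those limitations do concede that traffic pollution on the school commute, and time spent at other places, could not be accounted for. Commuting goes with school days. It builds up before the Friday sample and not over the weekend before the Monday one, so the contrast counts it as school exposure.

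At stake is what the trial may conclude. A Monday-to-Friday change could be taken as evidence of uptake in the classroom when the schedule cannot show that.

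**Working it through.** **No figure to reproduce.** The article gives no sample size, power or expected effect for the urine comparison, and no size for a morning-to-afternoon difference. The check is therefore one of estimability, followed by an illustration under stated assumptions.

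**Step 1: estimability.** Inputs: two sequences (Section 2.3), two intervention periods, and two sampling occasions per period (Section 3.2.2), giving 2 × 2 × 2 = 8 cells. The model columns are intercept, sequence, period, active, Friday/school, afternoon, and active × Friday.

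- With all 7 columns the design matrix has rank 6. Without the afternoon column it has rank 6 of 6.
- The school effect alone is not estimable, nor is the time-of-day effect alone. Their sum is.
- Active × Friday, the intervention-versus-sham difference in the Friday-Monday change, is estimable.

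The Friday/school column is also the weekday column, so weekday is aliased in the same way.

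**Step 2: what each contrast estimates.** On the log scale let s be the school effect, t the afternoon shift for non-school reasons, and e the intervention effect on the Friday value.

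- Friday − Monday under sham = s + t
- Friday − Monday under active = s + t + e
- Difference in changes = (s + t + e) − (s + t) = e
- Friday active − Friday sham = e

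**Step 3: illustration.** Assumed: t from −0.3 to +0.3, s of 0 or 0.2, e = −0.10, child SD 0.7, residual SD 0.5, and 50,000 simulated children per setting.

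| True s | Assumed t | Sham Friday − Monday | Difference in changes | Friday active − sham |
|---|---|---|---|---|
| 0 | −0.3 | −0.299 | −0.102 | −0.103 |
| 0 | 0 | −0.001 | −0.096 | −0.102 |
| 0 | +0.3 | 0.294 | −0.095 | −0.098 |
| 0.2 | −0.3 | −0.104 | −0.096 | −0.095 |
| 0.2 | 0 | 0.203 | −0.103 | −0.098 |
| 0.2 | +0.3 | 0.505 | −0.102 | −0.104 |

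The sham contrast follows s + t and can take the wrong sign. Both intervention contrasts stay near −0.10 throughout. The bias does not shrink with more children, because t enters every child's difference.

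**Step 4: the interval.** Monday of Week 1 to Friday of Week 2 is 11 days and spans about 5 + 5 = 10 school days with a weekend between. Section 6.2 describes the Friday sample as following 5 school days. The two accounts can be squared only if Section 6.2 means the second week alone, and it does not say so.

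**Step 5: what the Monday covariate can add.** In a simple two-group comparison with Monday-Friday correlation r (assumed), adjusting Friday values for Monday multiplies the variance of a Friday-only analysis by 1 − r²: 0.96, 0.91 and 0.75 at r = 0.2, 0.3 and 0.5. That is a reduction of 4%, 9% and 25%. In a within-child crossover the relevant correlation is between the period differences of the two samples. If r mostly reflects stable differences between children, the gain may be close to nil.

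**The case against.** The strongest reply is that the article claims less than it may seem to and already plans the sound comparison. Much of that stands.

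- **Wording.** A reader might infer that Section 6.2 claims to isolate school exposure. It does not. It speaks of distinguishing the two sources and of more accurate assessment, and it says openly that the Friday sample integrates home and school. It does, however, claim reduced out-of-school confounding as a property of the comparison, and the schedule does not provide that.
- **Interventions.** A reader might infer that the aliasing also defeats the intervention comparison. It does not. Both conditions use the same urine schedule, so an additive shift cancels, and Section 5.3 plans to compare internal exposure parameters between the two phases.
- **The Monday sample.** A reader might infer that it goes unused in the phase comparison. Section 5.3 does not say whether the tests use Friday values, changes or adjusted values. That detail may sit in a fuller document, so the silence is no finding.
- **Weight.** Urinary analyses are limited to Belgium and Denmark, and environmental monitoring is the primary exposure metric for the pooled analyses (Section 3.2.2). The primary outcomes are cognition and blood pressure (Section 4). The disputed sentence is in the Discussion.

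What the reply does not remove is the school-versus-home reading. That is an affirmative statement about the design, and because the aliasing lies in the sampling schedule, no unseen analysis plan could restore the missing information.

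**Conclusion.** The concern holds for the school-versus-home interpretation and not for the intervention effect. The aliasing of the Friday-Monday difference with time of day and weekday is complete and follows from the schedule alone. The mixing-in of commuting follows from the article's own limitations.

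The amount of bias is unknown. The ±0.3 log range is an assumption for illustration; since exp(0.3) = 1.35 and exp(−0.3) = 0.74, it means afternoon values about 35% higher or 26% lower. If the true morning-to-afternoon difference were nil, the time-of-day part of the bias would vanish, but the weekday and commuting parts would remain.

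The clean result for intervention versus sham assumes that the time-of-day effect is additive on the analysis scale and does not interact with treatment. The primary outcomes are untouched. The point is still worth correcting, because it changes what the biomarker data can be said to show.

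**What to change.** 1. Make the urinary-biomarker inference the intervention-versus-sham difference in the log Friday sample. Use a mixed model with treatment, period, the same-period log Monday sample as covariate, and the random intercepts already planned for school, class and child. Expect only a modest gain in precision from the covariate.
2. Report the Monday-to-Friday change as descriptive only.
3. In Section 6.2, replace the statement that the two samples separate school from home exposure and reduce outside confounding. State instead, as a limitation, that the two occasions differ in time of day and weekday and that the change also takes in commuting.
4. Reconcile the Section 6.2 description of 5 school days before the Friday sample with the Week 1 Monday to Week 2 Friday timing in Section 3.2.2.

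The cost is analysis specification and wording only; no new samples are needed. The downside is that the claim of separating school from home exposure is given up.

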## Conclusion

7

Here, we present a single-blinded crossover study protocol to investigate children’s indoor air exposure in primary schools in combination with an intervention of a novel air remediation strategy. The study will be conducted in Belgium, Denmark, and Greece using harmonized, standardized procedures. This approach measures and characterizes the levels and profiles of indoor air pollutants and microclimate parameters in schools, combined with the analysis of biomarkers of exposure, health parameters, and cognitive testing in children, to provide a comprehensive understanding of indoor air pollution in schools and its effects on children’s cognition, health, and well-being.

## Glossary

ANOVA: Analysis of Variance
BC: Black Carbon
BaP: Baseline Period
BP: Blood Pressure
BPV: Blood Pressure Variability
CO₂: Carbon Dioxide
DBP: Diastolic Blood Pressure
EU: European Union
FID: Flame Ionization Detector
GC: Gas Chromatography
GIS: Geographical Information Systems
HPLC: High-Performance Liquid Chromatography
HR: Heart Rate
IAQ: Indoor Air Quality
IP1: Intervention Period 1
IP2: Intervention Period 2
MS: Mass Spectrometry
NO₂: Nitrogen Dioxide
PAH: Polycyclic Aromatic Hydrocarbons
PM: Particulate Matter
PTFE: Polytetrafluoroethylene
SBP: Systolic Blood Pressure
SDT: Signal Detection Test
SOP: Standard Operating Protocol
SVOCs: Semi-Volatile Organic Compounds
UFP: Ultrafine Particles
UV: Ultraviolet
VOCs: Volatile Organic Compounds
WBGT: Wet Bulb Globe Temperature
WHO: World Health Organization
WP: Washout Period
